### Interventions

After obtaining actual caries data, schools with similar numbers of schoolchildren (at least 300 subjects per school) will be selected for the preventive project. The participants will be randomized, taking as cluster the school class, allocating each class into one of the two groups of the study (Fig. 1):

(1) The first group (Xyl) will receive sugar-free gums containing 70% (w/v) Xylitol as the only sweetener

(2) The second group (Pol) will receive reduced sugared gums containing 23% (w/v) Maltitol

Both groups of children will receive a total of 6 pellets of chewing gum a day during a period of one school year (about 9 months). All chewing gums will be produced and supplied by Perfetti Van Melle SpA (Lainate, Italy). All types of chewing gums will weigh 1.4 g each and will be identical in colour, shape and taste.

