#### Clinical examination

Clinical examination, coordinated by [name] as responsible of the coordinating centre, will comprise an oral examination (caries index, bleeding on probing recording) and an evaluation of plaque pH fluctuation after the sucrose challenge. Bleeding on probing will be used as a proxy of plaque presence, since there is a causal relationship between bleeding on probing and amount of plaque [13, 14].

The subjects will be examined using a mouth mirror, a ball-ended probe and artificial light. Caries registration will be performed with regard to the first and second primary, and first and second permanent, molars. The International Caries Detection and Assessment System (ICDAS) will be used to record caries at tooth level as initial, moderate or severe lesions, the number of filled teeth and the missing teeth for caries [15, 16]. Initial caries lesion can be defined as a primary lesion, which has not reached the stage of an established lesion with cavitation (ICDAS scores 1 and 2). Moderate caries lesions are defined as white or brown spot lesion with localized enamel breakdown or an underlying dentine shadow without visible dentine exposure (ICDAS scores 3 and 4). Extensive caries lesions are defined as a distinct cavity in opaque or discoloured enamel with visible dentine (ICDAS scores 5 and 6) [9, 15, 16]. The bleeding on probing score, as the percentage of periodontal site bleeding, will be registered in all subjects.

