#### Sample size

The sample size calculation was performed based on the primary outcome of the randomized clinical trial (caries increment at enamel and dentinal level). The calculation considered the results of a 3-year period [7, 8]. It was also taken into account an increment of approximately 10% of the sample due to some changes in the prevalence of the disease. Thus, estimating a level of significance of 0.05 with a power of 80% and a caries prevalence of about 90% [5], the number of participants was set to 409 subjects (Kelsey method), based on a 10% absolute difference between the groups, using a two-tailed test [19].

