### Data collection, management, and analysis

The follow-up assessments will be performed by calibrated blinded dentists. The clinical data will be recorded on electronic sheets organized on PageMaker and then transferred into Microsoft Excel Software. The data management team is formed by two authors ([name], [name]). Data will be cleaned, deleting those revealing the participants’ identities, and they will be shared in a public repository at the moment of the submission of the manuscripts.

Data on caries will be recorded considering the tooth as the unit of analysis. The progression or change of status can be described with three modalities: 1—as the change from no caries stage to initial stage or to moderate stage or extensive; 2—as the change from initial stage to moderate or extensive stage; and 3—as the change from moderate stage to extensive stage. The net caries increment for initial, moderate and extensive caries levels, using ICDAS (Δ-initial, Δ-moderate and Δ-extensive), will be calculated in primary and permanent molars. Differences between groups in terms of caries increment will be evaluated using the nonparametric Mann–Whitney *U* test. Data analysis will be conducted through Kaplan–Meyer graphs to evaluate caries increment. A comparison of the methods will be carried out with Cox regression with shared frailty. The calculation of sensitivity, specificity and accuracy will consider the results obtained with the indices and the classification of caries lesion presence by the proposed reference standard. The cost-effectiveness ratio will also be verified, considering as effectiveness the prevention of the primary outcome. For all tests, two-tailed analyses will be used, considering a level of significance of 5%. The quality-adjusted life-year index (QALY) will be calculated to assess the value of the preventive intervention [22]. To determine QALYs, the utility value associated with a given state of health by the years lived in that state will be calculated. A year of life lived with no caries increment will be worth 1 QALY (1 year of life × 1 utility value) [22, 23]. Plans to promote participant retention and completion of follow-ups will be performed; a list of any outcome in participants who discontinue the treatment will be compiled and the data will be analysed, taking into account that living conditions in Ladakh do not allow for high mobility of the population. This will make participant retention a minor problem.

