The effectiveness of the treatment will be assessed for those who fully followed the protocol (per-protocol subjects). The efficacy and consequences of treatment will be also considered, calculating the event rate (ER) for each group and the number needed to treat (NNT) [24]. An event will be defined as the change of status at tooth level, i.e. the development of a new lesion or the progression of an existing lesion to a more severe level or the change of a tooth previously affected in a filled or a missing tooth during the 2-year follow-up period.

Analyses will be performed using the statistical package Stata 16.0 (Stata Corp, College Station, USA).

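### The NNT rests on an event defined per tooth, so on the plain reading it counts teeth, although children are treated and classes randomised

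*Protocol article*

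**What the plan says.** Under Data collection, management, and analysis, the article plans efficacy measures by "calculating the event rate (ER) for each group and the number needed to treat (NNT"). The next sentence supplies the event: "An event will be defined as the change of status at tooth level". It covers a new lesion, progression to a worse level, or an affected tooth becoming filled or missing, all "during the 2-year follow-up period". Earlier in the same section: "Data on caries will be recorded considering the tooth as the unit of analysis".

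The treated and randomised units are different. Under Interventions, "Both groups of children will receive a total of 6 pellets of chewing gum a day", and "The participants will be randomized, taking as cluster the school class, allocating each class into one of the two groups of the study". Each child contributes several teeth: "Caries registration will be performed with regard to the first and second primary, and first and second permanent, molars" (Clinical examination). The number of molars present per child is not given.

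No section defines a child-level event, such as at least one affected molar. None converts a tooth result into children for the NNT, and no ER or NNT value is given or assumed.

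**The concern.** An NNT is the reciprocal of a risk difference, and its unit is whatever the risk is a proportion of. Here the event is a change in one tooth and the tooth is the unit of analysis, so the reciprocal difference is a number of teeth. Chewing gum is not given to teeth. Two child-based quantities would be useful: the children treated to spare one child any event, and the children treated to prevent one tooth event. A tooth-level NNT is neither of these.

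The article says that the findings should strengthen the evidence for community-based prevention programmes in children (Discussion). An NNT reported there without a unit would naturally be taken to mean children. The reader could not correct it, because the ratio between the tooth and child figures depends on the number of molars and on how events cluster within a child.

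**Working it through.** **Plan's own figures.** There is no ER or NNT to reproduce. The nearest figure is the sample size of 409 subjects, based on a 10% absolute difference with "estimating a level of significance of 0.05 with a power of 80% and a caries prevalence of about 90"%. Kelsey's formula with 90% v 80% gives, per arm, (1.960 + 0.842)² × 0.85 × 0.15 × 2 / 0.10² = 200.1, rounded up to 201. That is 402 in total before the stated increment of about 10%, close to 409 but not equal to it. (With the increment it is 443; that is a separate matter.) The relevance here is only that the trial is sized on a difference in proportions of subjects. A 10% difference on that scale corresponds to 1/0.10 = 10 children.

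**Inputs for the illustration.** All are assumptions, because the article gives none of them: control and xylitol tooth event rates p0 and p1; molars per child m = 8 or 12; within-child correlation ρ = 0.05, 0.10, 0.20 and 0.30.

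**Formulas.**
- Tooth NNT = 1/(p0 − p1).
- Children treated per tooth event prevented = 1/[m(p0 − p1)].
- Child NNT = 1/(R0 − R1), where R is the risk that a child has at least one event. Under a beta-binomial model, R = 1 − Γ(b+m)Γ(a+b)/[Γ(b)Γ(a+b+m)], with a = p(1−ρ)/ρ and b = (1−p)(1−ρ)/ρ.

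**Worked case: 20% v 15%, m = 8.**
- Tooth NNT = 1/0.05 = 20.
- Children per tooth event prevented = 1/(8 × 0.05) = 2.5.
- At ρ = 0.10, R0 = 0.727 and R1 = 0.614. The difference is 0.113, so the child NNT is 8.9.
- At ρ = 0.30, R0 = 0.564 and R1 = 0.458. The difference is 0.106, so the child NNT is 9.4.

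**Results over ρ = 0.05 to 0.30.**

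| Tooth rates | Molars | Tooth NNT | Child NNT | Children per tooth event prevented |
|---|---|---|---|---|
| 20% v 15% | 8 | 20 | 8.9–9.4 | 2.5 |
| 30% v 25% | 8 | 20 | 13.7–18.9 | 2.5 |
| 30% v 25% | 12 | 20 | 14.6–31.0 | 1.7 |
| 10% v 8% | 8 | 50 | 12.8–17.4 | 6.25 |

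Read as children, the tooth figure is about 2.2-fold too high in the first row (20/8.9). In the third row, at ρ = 0.05, it is about 1.5-fold too low (31.0/20). In the last row it is up to about 4-fold too high (50/12.8). The ratio of the tooth NNT to the last column is simply m, so it restates the assumed molar count and adds no evidence.

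**Ceiling check.** At 30% with ρ = 0.05, the control risk of at least one event is 0.91 with 8 molars and 0.96 with 12. The child-level difference is then squeezed (0.032 with 12 molars), and this is what drives the child NNT up to 31.

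**The case against.** The strongest reply is that the denominator is inferred. The article says what counts as an event but never says that the ER is events divided by teeth. Scoring at tooth level may only describe where a change is recorded, with each child then classed as having an event or not. The paragraph opens with per-protocol subjects, and the sample size is in subjects; both suit a child-level proportion. The ER and NNT also cite a methods reference that is not available here. This stands in part. It rules out saying that the plan will certainly report a wrong number. It does not clear the text, because the tooth is the only unit named for both the event and the analysis, and no child-level event is defined. Dividing tooth events by children would not give the usual NNT either: that rate is a mean count that can exceed 1, and its reciprocal difference is children per tooth event prevented.

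A second reply is that teeth needed to avoid one tooth event is a coherent quantity if labelled so. That is true, but the article attaches no such label.

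Third, a reader might infer that the NNT's confidence interval would ignore the clustering of teeth within children and children within classes. The documents do not support that. No interval for the NNT is described, interval methods are commonly left to the analysis plan, and shared frailty is planned for the Cox model.

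Finally, a child-level event has its own weakness, the ceiling shown above. This stands, and it is why the fix asks for a second measure.

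**Conclusion.** The point holds for a supplementary measure. The event behind the ER and NNT is fixed at tooth level while children are treated, so on the plain reading the NNT is a number of teeth and answers neither child-level question. It would be wrong to infer that the primary comparison or the sample size is undermined; neither uses the NNT.

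The size is illustrative only. Under the assumed rates, molar counts and correlations, the tooth figure ranges from about 4-fold too high to about 1.5-fold too low when read as children. A reader might also quote an 8- to 12-fold error on the reading of children per tooth event prevented. That figure only restates the assumed 8 to 12 molars, and 12 is a deliberately high value. What does not depend on the chosen rates is that the units differ and that no reader can convert one to the other without child-level data.

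**What to change.** In the paragraph that defines the event, state that the ER and NNT are computed on children: a child has an event if at least one scored molar changes status within the stated window. Take the NNT from the difference in child-level risk, and give any interval with allowance for clustering by school class.

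State one window. The paragraph refers to two years, whereas Participant timeline enrols each child for 36 months (9 of treatment and 27 of follow-up) and Implementation places the last examination at the third 12-month visit. The two should be reconciled explicitly.

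Because an any-molar event may approach a ceiling when tooth rates are high, also report tooth events prevented per 100 children treated. In the worked case this is 100 × 8 × 0.05 = 40. Do not present a tooth-level figure as an NNT.

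The cost is a few sentences and a different denominator. The examinations already score each child's molars, so no new data are needed.

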#### Eligibility: inclusion and exclusion criteria

The inclusion criteria will consider the following:

a) To be 5–14 years old

b) To be in good general health

The exclusion criteria will consider the following:

a) Children who refuse to participate in the research; parents/guardians who refuse the participation of their children to the trial

b) Children who present systemic conditions or chronic diseases that require differentiated care and follow-up

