#### Preliminary epidemiological survey

A team of four dentists received training to diagnose caries lesions using the WHO-DMFT index for permanent teeth and the dmft for primary teeth. The team received training, and inter-examiner reliability was assessed before the start of the study; sensitivity, specificity, percentage agreement and kappa statistics were recorded. Inter-examiner reliability ranged from 0.75 to 0.84 (K-Cohen) for sound teeth and from 0.82 to 0.88 for caries lesions. Intra-examiner reliability ranged from 0.82 to 0.90 for sound teeth and from 0.84 to 0.91 for caries lesions. Dental caries prevalence (dt/DT) and severity (number of lesions) were recorded for caries at the dentinal lesion level [12]. Every subject was examined using a plain mirror (Hahnenkratt, Königsbach, Germany) and the WHO CPI ballpoint probe (Asa-Dental, Milan, Italy), under standard light. No bitewing radiographs or fibre-optic trans-illumination were used.

An ad hoc prepared questionnaire assessed general health, eating habits, oral hygiene and the self-perception of oral conditions, based on previous surveys [12, 13]. The height (cm) and the weight (kg) were measured and the body mass index (BMI) was calculated. The waist circumference was also measured.

Caries was almost ubiquitarian with only 10.04% of caries-free children (dt/DT = 0). Caries severity, in both primary and permanent dentitions, was statistically significantly related to gender and waist circumference (*p* < 0.01). This preliminary epidemiological survey will allow to design the intervention trial.

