#### Ancillary and post-trial care

Parents/guardians of the children participating in the trial will receive information about the children’s oral status. If caries lesions in dentine will be detected in the children enrolled in the trial, the children will insert in a treatment plan list and they will be contacted for cares by the medical centre in Padum (CHC, community health centre).

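### The event rule counts an already carious molar that is filled or lost without any progression, so treatment of baseline lesions enters the event rate and NNT and dilutes the contrast

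*Protocol article*

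**What the plan says.** All references are to the protocol article.

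- **Event definition** (end of Data collection, management, and analysis). The event rate per group and the NNT are introduced, and the next sentence defines an event as a change of status at tooth level. There are three alternatives joined by *or*: a lesion that newly appears, a lesion that worsens in stage, or "the change of a tooth previously affected in a filled or a missing tooth during the 2-year follow-up period".
- **Progression** (same section, earlier). Three kinds of stage change are listed: from sound to any lesion stage, from initial to moderate or extensive, and from moderate to extensive. Filled and missing are not among them. Net increments by stage are compared with the Mann–Whitney test. Kaplan-Meier and shared-frailty Cox analyses are also named, with no event of their own.
- **Recording of teeth** (Clinical examination). The teeth are the "first and second primary, and first and second permanent, molars". The examination also records "the number of filled teeth and the missing teeth for caries".
- **Care during the trial** (Ancillary and post-trial care). "If caries lesions in dentine will be detected in the children enrolled in the trial, the children will insert in a treatment plan list". The Padum health centre then gets in touch with them about treatment.
- **Disease at entry** (Preliminary epidemiological survey). "Caries was almost ubiquitarian with only 10.04% of caries-free children", measured at the dentine level.
- **Duration** (Participant timeline). Each child is enrolled for 36 months, 9 of treatment and 27 of follow-up. The event definition speaks of two years.

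**The concern.** A caries-prevention endpoint should register disease that arises or worsens after allocation. The third alternative registers something else: a tooth that was already diseased has been treated or lost. The lesion may be unchanged since baseline.

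The trial's own examinations help to produce this change, because a dentine lesion found in an enrolled child leads to the treatment list. Since most children in the preliminary survey had at least one dentine lesion, the pool of teeth that could become events this way may be large.

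If treatment is equally common in both arms, the extra events add noise to both and shrink the risk difference, which costs a superiority trial power and inflates the NNT. If treatment differed between arms, for instance because access differs between classes, it would add a difference unrelated to xylitol. The documents give no sign that it does differ.

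**Working it through.** **1. What the rule does to each type of tooth**

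| Molar at baseline | Event through disease | Event through filling or loss alone |
|---|---|---|
| Sound | New lesion | No (not previously affected) |
| Initial | Progression | Yes, even without progression |
| Moderate | Progression | Yes, even without progression |
| Extensive | None possible: top stage | Yes; the only route |

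The last row is the clearest case. For teeth extensive at baseline, the endpoint can measure only care received or tooth loss. A filling cannot stand in for unseen progression to a worse stage, because no worse stage exists.

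**2. Which analyses are reached**

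The definition is attached in the text to the event rate and the NNT. The Kaplan-Meier and Cox analyses also need an event, and this is the only one in the document, but no sentence says that they use it. The stage-change list used for increment leaves out filled and missing.

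**3. The plan's sample size, as a base for the illustration**

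Inputs from Sample size: two-sided 0.05, power 80%, prevalence about 90%, absolute difference 10 points, Kelsey method. I take 0.90 against 0.80 with equal arms.

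n per arm = (1.960 + 0.842)² × p̄(1 − p̄) × 2 / d² = 7.85 × 0.85 × 0.15 × 2 / 0.01 ≈ 200.1, rounded up to 201. The total is 402, against the stated 409. The figure is close enough to confirm these inputs, provided the 10% increment mentioned there was not added on top (402 × 1.1 = 442).

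**4. Dilution**

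Let p be the true event probability and q the probability that an otherwise event-free unit becomes filled or missing, equal in both arms. The observed rate is p* = p + (1 − p)q. The observed difference is therefore (p₁ − p₂)(1 − q), and the NNT is its reciprocal.

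Power uses n = 204 per arm (409 / 2) and the usual normal approximation, Φ{[d√n − 1.96√(2p̄(1 − p̄))] / √(p₁(1 − p₁) + p₂(1 − p₂))}. It ignores clustering by class.

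| q (assumed) | Observed rates | Difference | NNT | Power |
|---|---|---|---|---|
| 0 | 0.90 / 0.80 | 0.10 | 10.0 | 81% |
| 0.1 | 0.91 / 0.82 | 0.09 | 11.1 | 76% |
| 0.2 | 0.92 / 0.84 | 0.08 | 12.5 | 70% |
| 0.3 | 0.93 / 0.86 | 0.07 | 14.3 | 64% |
| 0.5 | 0.95 / 0.90 | 0.05 | 20.0 | 48% |

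The sample size for equal power scales with p̄(1 − p̄)/d²:

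- q = 0: 0.85 × 0.15 / 0.10² = 12.75.
- q = 0.1: 0.865 × 0.135 / 0.09² = 14.42, a ratio of 1.13.
- q = 0.2: 0.88 × 0.12 / 0.08² = 16.5, a ratio of 1.29.

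**5. Limits of the illustration**

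No document gives q. The clause covers only previously affected teeth, so q is the share of event-free units that were affected multiplied by the share of those that are then filled or lost. The 90% is a child-level prevalence used for planning, while the event is at tooth level.

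**The case against.** The clause has a purpose. Examinations are yearly (Implementation), so a lesion that progresses and is filled between visits would otherwise be missed. Treatment may also be rare: the Introduction describes care limited to small clinics, with volunteer dentists in summer, and the ancillary-care section gives neither timing nor completion rate. Both points stand. They leave the size of the problem open, but they do not rescue the rule for a tooth that was extensive at baseline, or for one filled at an unchanged stage.

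Several stronger readings are tempting, and the documents do not support them:

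- **That such teeth are scored in the primary caries increment.** The event is tied explicitly only to the event rate and NNT. Its use in the Kaplan-Meier and Cox analyses is an inference.
- **That natural shedding of primary molars is an event.** The definition omits the cause of loss, but the examination records teeth missing because of caries, which would exclude shedding if applied. A sound molar that is shed is not covered at all. This is an ambiguity. That primary molars are shed at these ages (eligibility is "To be 5–14 years old") is general knowledge and is not stated in the protocol.
- **That a filled extensive lesion lowers the net extensive increment**, so that two analyses score one tooth in opposite directions. The protocol does not say how filled teeth enter the net increment.
- **That about 90% of study molars are affected.** The survey figure is the share of children with any dentine lesion.
- **That the required sample rises 1.4-fold to 2.0-fold.** That needs assumed rates such as 30% against 20%, which appear nowhere in the protocol. The planning rates give about 1.13-fold and 1.29-fold for the same q of 0.1 and 0.2.

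**Conclusion.** The concern holds for the event definition as written. A previously affected tooth that is filled or lost is an event without progression and without a caries-related reason, and the trial refers dentine lesions for treatment. Prevalent disease therefore enters the event rate and the NNT. It enters the Kaplan-Meier and Cox results only if they share this event.

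The direction is clear if treatment is similar in both arms: the risk difference shrinks by (1 − q). The size cannot be established from the documents. For an assumed q of 0.1 to 0.2 on the planning rates, 10 points become 9 to 8, the NNT rises from 10 to 11.1 to 12.5, and power falls from 81% to 76% to 70% before any allowance for clustering.

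The definition should be changed before recruitment starts.

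**What to change.** Reword the event definition in Data collection, management, and analysis:

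1. Take teeth that are extensive, filled or missing at baseline out of the event risk set.
2. For other teeth, count filled or missing-for-caries as an event only if a new lesion or progression since baseline was documented, or if the tooth was sound or initial at the previous examination. Admitting every moderate tooth here would not be enough, because a baseline moderate lesion filled without progression would still count.
3. Report restorations and extractions of baseline lesions without documented progression separately, with a sensitivity analysis that counts them as events.
4. Carry the caries qualifier for missing teeth from Clinical examination into the event definition, and censor naturally shed primary molars at their last examination.
5. State whether the Kaplan-Meier and Cox analyses use this event.
6. Reconcile the two-year period in the definition with the 36 months in Participant timeline.

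The cost is rewording. ICDAS stage at baseline and teeth missing because of caries are already to be recorded, and Trial status says that recruitment has not started. The price is a small loss of events, including some lesions that progress and are filled between yearly visits; the sensitivity analysis shows how much this matters. Nothing here changes the care offered to the children.
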